## Subject data protection

The ICF will incorporate wording that complies with relevant data protection and privacy legislation. Pursuant to this wording, subjects will authorize the collection, use and disclosure of their study data by the investigator and by those persons who need that information for the purposes of the study.

The ICF will explain that study data will be stored in a computer database, maintaining confidentiality in accordance with national data legislation.

The ICF will also explain that for data verification purposes, authorized representatives of the Sponsor, a regulatory authority or an EC may require direct access to parts of the hospital or practice records relevant to the study, including subjects’ medical history.

The Investigator must file a Subject Identification List which includes sufficient information to link records, *i.e.*, the CRF and clinical records. This list should be preserved for possible future inspections/audits but should not be made available to the Sponsor except for monitoring or auditing purposes.

## Protocol deviations and amendments

Modifications to the signed protocol are only possible through approved protocol amendments and with the agreement of all responsible persons. Details of non-substantial amendments are to be clearly noted in the amended protocol.

A change that concerns; a new trial site, new principal investigator and/or a new informed consent form should only be submitted to the concerned EC.

In case of a substantial protocol amendment (e.g. change of; main purpose of the trial, primary/secondary variable, measurement of primary variable, investigational product, or dosing), the concerned EC and CA must be informed and should be asked for its opinion/approval prior implementation of amended protocol, as to whether a full re-evaluation of the ethical aspects of the study is necessary by the committee. This should be fully documented.

The Investigator must not implement any deviation from, or change to, the protocol without discussion with, and agreement by the Sponsor and prior review and documented approval/favorable opinion of the amendment from the relevant EC and CA, except where it is necessary to eliminate an immediate hazard to study subjects, or where the change(s) involves only logistical or administrative aspects of the study (*e.g.* change in monitor(s), change of telephone numbers).

# Quality control and quality assurance

## Training of study site personnel

It is the responsibility of the Principal Investigator to ensure that all personnel involved in the study are fully informed of all relevant aspects of the study and have a detailed knowledge of and training in the procedures that are to be executed by them. Any new information of relevance to the performance of this study must be forwarded to the staff involved in a timely manner.

The Investigator will keep a list of all personnel involved in the study together with their function and study related duties delegated. A Curriculum Vitae (CV) will be available for all staff delegated study-specific duties.

## Clinical Monitoring

The monitor will have regular contacts with the clinic to verify informed consents of participating subjects, to confirm that facilities remain acceptable, that the investigational team is adhering to the protocol and GCP, that data are being accurately recorded in the CRFs, to verify inclusion/exclusion criteria, study main endpoints, check AE/SAE reporting and that therapy accountability is being carried out. The investigator should ensure that all persons assisting with the trial are adequately informed and trained about the protocol, the investigational product and their trial related duties and functions. The monitor will check that training has been performed and that this is documented. The monitor will also ensure source data verification (comparison of the data in the CRF with the medical records and other source data). The monitor must have direct access to source data. The extent of monitoring will be defined in a monitoring plan.

## Audits and inspections

The purpose of an audit or inspection is to systematically and independently examine all study-related activities and documents, to determine whether these activities were conducted, and data were recorded, analysed, and accurately reported according to the protocol, current ICH-GCP guidelines and any applicable regulatory requirements. The Investigator will permit trial-related audits or inspections at the research clinic, including Source Data Verification (SDV), by authorised representatives of Sponsor, a CA, or an EC. The Investigator must ensure that all source documents are accessible for auditing and inspection. The Investigator is required to inform the Sponsor immediately of an inspection requested by a CA or an EC.

# DATA MANAGEMENT

All data should be recorded, handled and stored in a way that allows its accurate reporting, interpretation and verification.

## Source data

Source data are original documents, data and records. The investigator must, for each subject in the study, maintain adequate and accurate source documents, such as medical records, ICF, completed rating scale forms, etc. Changes to source data should be traceable, should not obscure the original entry, and should be explained if necessary. A source data verification log will be included in the Investigator Study File (ISF). The investigator must ensure that all source documents are accessible for monitoring.

## Case Report Form

The investigator will ensure that all data collected in the study are recorded in the CRF in a timely manner according to any instructions provided.

An electronic Case Report Form (CRF) will be used for data collection. Only the Investigator or persons authorised by the Investigator are allowed to make entries to the CRF. The Investigator will ensure that the data is recorded in a timely manner and in accordance with the instructions provided. The Investigator is responsible for the accuracy and completeness of the data entered and sign off the completed CRF. A copy of the completed CRF will be archived at the study site.

## Data Management Plan

Data management refers to the activities for efficient and correct entering of subject information into a database and confirming data accuracy. Detailed information on data management will be described in a study-specific Data Management Plan (DMP) and Data Validation Plan (DVP).

Staff designated by Gothia Forum and working on behalf of the Sponsor will review the data entered into the CRFs by investigational staff for completeness and accuracy and instruct the site personnel to make any required corrections or additions. Queries are issued electronically. Designated investigator site staff is required to respond to the query and confirm or correct the data.

At the conclusion of the study, the occurrence of any protocol deviations will be determined. After these actions have been completed and the database has been declared to be complete and accurate, it will be locked and available for data analysis.

## External Data

External data consists of data that is not recorded in CRFs. Data may be received in electronic format or paper printout. Key variables are defined in order to uniquely identify each sample record. File and data formats are agreed with the external data provider. Any electronically transferred data must contain origin, date created, date sent and number of records at minimum. External data will be entered into the CRF by the Investigator or designee.

## Archiving

The Principal Investigator is responsible for maintaining essential documents, (as defined in ICH E6 GCP, Section 8) for at least 10 years after finalisation of the Clinical Study Report (CSR), in accordance with Swedish regulation/law (Chapter 10, 3 § in LVFS 2011:19). This includes any original source documents related to the study, the Subject Identification List (providing the sole link between named subject source records and anonymous CRF data), the original signed ICFs and detailed records of disposition of IMP.

It is the responsibility of the Sponsor to inform the Investigator/institution as to when these documents no longer need to be retained.

The Sponsor will archive the *Trial Master File* in accordance with ICH E6 GCP, Section 8 and applicable regulatory requirements.

# STATISTICAL METHODS AND DETERMINATION OF SAMPLE SIZE

The principal features of the statistical analysis to be performed are described in this section. A more technical and detailed elaboration of the principal features will be prepared before study data analysis in a separate Statistical Analysis Plan (SAP) which will be signed and approved by the sponsor.

## General

Pharmacokinetic data will be presented using summary statistics. Data will be presented in terms of number (N), arithmetic mean, standard deviation (SD), median, minimum and maximum value. In addition, for the parameters AUC and Cmax the geometric mean and coefficient of variation (CV) will be presented.

Categorical data will be presented as counts and percentages. When applicable, summary data will be presented by assessment time. Individual subject data will be listed by subject number and, where applicable, by assessment time.

## Sample size determination

No formal sample size calculation has been performed for this study. The proposed sample size is considered sufficient in this early phase II development to provide adequate information on the patients.

## Analysis data sets

The full analysis set for efficacy analysis is defined as all subjects who took at least one dose of IMP and with at least one efficacy measurement.

The safety analysis set will consist of all subjects who took any IMP.

No Per Protocol Set will be created and analysed.

## Description of study population

### Demographics and other baseline characteristics

Demographics and other baseline characteristics will be presented using summary statistics.

### Medical history and prior/concomitant medication

Medical/surgical history and prior/concomitant medications will be presented by descriptive statistics and listings.

### Study termination

The reason for study termination and number of subjects who completed the study will be presented with frequency tables.

## Analysis of primary endpoints

### Vital signs (blood pressure, heart rate and body temperature).

Vital signs (blood pressure, heart rate and body temperature) will be presented by visit for each parameter and subject and summarised using summary statistics including absolute and percent change since baseline.

### Physical examination

Abnormal findings will be specified and presented by subject and summarised by frequency tables.

### ECG

All ECG data will be listed for each subject and summarised as the vital signs parameters including absolute and percent change since baseline using summary statistics. In addition, ECGs will be categorised as: “normal, abnormal, not clinically significant”, or “abnormal, clinically significant” (as judged by the Investigator) and summarised by visit.

### Safety laboratory analyses

Safety laboratory data will be presented by visit for each parameter and subject and summarised using summary statistics including absolute and percent change since baseline.

#### AEs

AEs and SAEs will be recorded from start of IMP administration until the end of study follow-up visit (Visit 9). AEs that occur before first treatment with IMP will be reported separately as baseline events.

All AEs will be described in terms of treatment/dose at which they occurred. AEs will be summarised by Preferred Term (PT) and System Organ Class (SOC) using the MedDRA vocabulary. The number of subjects reporting AEs, and the number of AEs reported will be presented. The events will be tabulated by SOC, PT and by severity and relationship to IMP. SAEs will also be presented in separate tabulations. The number of subjects experiencing an AE in connection to the treatment will be presented using descriptive statistics.

## Efficacy endpoints

### Functional rating with ALSFRS-R and Norris scales

Both these scales will be reported according to the manuals with changes from baseline using summary statistics.

### Evaluation of biomarkers for neurological disorders

All biomarkers will be presented using summary statistics with changes from baseline for each visit.

### Pulmonary function (FVC)

The FVC values at baseline and subsequent visits will be presented using summary statistics with changes from baseline.

### Levels of Hepatocyte Growth Factor (HGF)

The levels of HGF will be presented by subject and assessment time using summary statistics with changes from baseline.

### Changes in APTT (effect APTT)

The APTT will be presented by subject and assessment time using summary statistics with changes from baseline.

### Pharmacokinetics of ILB

Individual plasma concentration-time data of ILB will be evaluated using a validated Phoenix WinNonlin software. The pharmacokinetic (PK) analysis (non-compartmental analysis, NCA) will consist of assessment of PK parameters including at least: C_max_, t_max_, t_last_, AUC_last_, AUC_tau_, AUC_(0-t)_, AUC_inf_, t_½_, λz, Rac_obs_, if data permits. Other additional parameters may be assessed as considered appropriate.

## Statistical/analytical issues

### Adjustments for covariates

Not applicable.

### Handling of dropouts or missing data

There will be no analysis done to correct for missing data such as Last Observation Carried Forward, *i.e.* only data present will be used in the analyses.

### Multiple comparison/multiplicity

Not applicable

### Interim analyses and data monitoring

An interim analysis may be performed after half of the study population (6-8 patients) have completed visit 7 to assess futility and safety on the group level. Analysis will be performed for the safety variables, disease severity, biomarkers for neurological diseases including NFL and pulmonary function.

# insurance and financing

## Insurance

The Sponsor agrees to indemnify and hold the Investigator free of harm from any claim, whether based on legal principles or on generally accepted liability standards within the pharmaceutical industry, made against him/her by reason of personal injury, including death, to any person arising out of or connected with the performance of the study to the extent the injury is not cause by:

- Failure by the Investigator to adhere to the terms of the study protocol
- Failure by the Investigator to comply with any applicable governmental regulations
- Malpractice, negligence or wilful malfeasance by the Investigator

The sponsor’s responsibility is covered by the insurance “LIF Läkemedelsförsäkring”.

The study subjects are covered by the Swedish Patient Injury Act and the Pharmaceutical Insurance (<http://lff.se/>). The insurance also covers the sponsor’s liability under law and generally accepted liability standards within the pharmaceutical industry towards any third parties, including subjects as sponsor of the study. The study will not be initiated before proof of this insurance is fulfilled.

In addition, all subjects are covered by the general insurance for patients treated at Swedish medical instances (“Patientförsäkringen”).

## Financing

Details regarding economy will be separately addressed and agreed between the Sponsor and the clinical hospital research unit, the investigators and consultants for medical and clinical management before initiation of the study.

# Study timetable and discontinuation

The study will commence as soon as the CA and the EC have approved the study, as soon as patients have been recruited and as soon as contracts between the Sponsor and all parties have been signed.

The end of the clinical part of the study is defined as the last visit of the last subject participating in the study.

The study is expected to start in Quarter 2, 2018 and to be completed by Quarter 4, 2019.

The Sponsor reserves the right to discontinue the study at any time, but intends only to exercise this right for valid scientific or administrative reasons.

After such a decision, the Investigator must inform all participating subjects and perform relevant assessments, preferably according to the scheme for the final assessments. All delivered and unused study products and other study materials must be returned and all CRFs completed as far as possible.

In the case of early termination, the sponsor must notify the end of the trial to the CA and the EC immediately and at the latest within 15 days after the trial is halted, clearly explain the reasons, and describe follow-up measures, if any, taken for safety reasons.

# Publication policy

As soon as the clinical study is approved by the CA the study is automatically registered in a publicly accessible database before recruitment of the first subject.

After completion of the study, the sponsor will prepare a Clinical Study Report (CSR) in cooperation with the Investigator. The sponsor is responsible for submitting the final version of the CSR to the CA within 12 months after the end of trial notification.

The CSR will form the basis for manuscripts intended for publication in a medical journal. Attempts to publish negative or inconclusive as well as positive results must be made, or otherwise made publicly available. Formal presentation or publication of data collected in this study should be considered as a joint publication by the sponsor and the clinical investigators. The Principal Investigator will be asked to be a part of the authorship. Authorship will be determined by mutual agreement, where one part will be lead author and the others; co-authors. Before any publication (oral or written) of the results, the co-authors will be given 30 days for review and comment on the manuscript. If the lead author has not submitted the results for publication within 6 months after completion of the final CSR, the co-authors have the right to publish as lead authors. In this event, the other part is considered co-author and will be given 30 days to review and comment on the manuscript before it is submitted to a journal. If the findings of the study are of a varying character with diverse matters of results, the data should be made public in several publications with different aspects of the results. In that case, the order of the authors of the different publications will be made in relation to the contribution of work made by the different authors according to the international rules of publication. The costs of publication will be covered by the Sponsor.

# APPENDIX

## Appendix 1. Risk management

| **Risk** | **Grade** | **Clinical sign/value** | **Treatment plan** |
| --- | --- | --- | --- |
| Lung function  Microspirom. | A | No particular signs. | None |
|  | B | Results outside normal ref. range | Observation |
|  | C | Variation >10% between time points | Observation/additional measurements and follow-up |
| Platelet depletion | A | No particular signs. | None |
|  | B | A reduction of >50% from baseline platelet count or ˂ 150x10^9^/L. | Observation |
|  | C | ˂50x10^9^/L, petechial or mucosal bleedings | Observation, consider optimal intervention |
| Bleeding | A | No particular signs. | None |
|  | B | A reduction of haemoglobin of >20g/L, but without clinical signs such as a rise in pulse or drop in blood pressure.  Surgicutt > 900s. | Observation |
|  | C | A reduction of haemoglobin of >20g/L together with clinical signs such as a rise in pulse or drop in blood pressure. Apparent bleeding. | Observation.  1. Stop further administration of ILB.  2. Buffer and/or plasma expander infusion.  3. Transfusion of erythrocytes, fresh frozen plasma and platelets.  4. Administration of Prothrombin complex or FVIIa (NovoSeven®).  5. Surgical intervention if severe bleeding cannot be stopped by steps 1-4 |
| Allergic reactions | A | No particular signs. | None. |
|  | B | Clinical symptoms in combination with blood pressure drop (systolic ˂100) or pulse below 50 beats/min.  Irritation of airways. | Observation. Optimal treatment with adrenaline or steroids. |
|  | C | Blood pressure drop (systolic ˂80) or pulse below 45 beats/min.  Affected breathing. | Try to differentiate from bleeding. Consider optimal treatment with adrenaline and steroids. |
| Out of reference values / Adverse Event (AE) | A | Safety parameters outside the reference ranges/other clinical findings which constitute a medical significant risk. | Observation/treatment suitable for treating the AE condition. |
|  | B | Reaction defined as a SAE. | The event will be observed and reported according to protocol. PI is responsible for the evaluation. |

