| **Safety and efficacy assessments**  Safety:   - AE assessments will start at administration of the first dose of ILB. - Physical exam will be obtained at all visits. On the days of ILB administration (Visit 2 to Visit 6), physical examination will be obtained before dosing. - Vital signs (blood pressure, heart rate and body temperature) will be obtained at all visits. - 12-lead ECG will be obtained at Visit 1 and Visit 7. - Lab tests (clinical chemistry, haematology, haemostatis) will be obtained at all visits. On the days of ILB administration (Visit 2 to Visit 6), lab tests will be obtained before dosing.   Efficacy:   - The investigator will complete the ALS Functional Rating Scale - Revised (ALSFRS-R) at all visits. On the days of ILB administration, rating scales will be completed before dosing. - The investigator will complete the Norris functional rating scales at all visits. On the days of ILB administration, rating scales will be completed before dosing. - Blood and cerebrospinal fluid (CSF) samples for evaluation of the ALS biomarker Neurofilament Light chain (NFL) will be obtained at Visit 1 after eligibility is confirmed and at Visit 7. - Blood and CSF samples for analysis of biomarkers for neurological disorders (see 11.4.2) will be obtained at Visit 1 after eligibility is confirmed and at Visit 7. - Respiratory function (FVC) will be evaluated at all visits. On the days of ILB administration (Visit 2 to Visit 6), respiratory function will be assessed before dosing. - Quality of Life (QoL) will be evaluated using Visual Analogue Scale (VAS)-based questionnaire filled out by patient and, if applicable, a next of kin, at Visit 1, Visit 2, Visit 4, Visit 6 and Visit 8. - Autonomous symptoms will be evaluated according to a 4-grade scale for a range of parameters at all visits. - Levels of Hepatocyte Growth Factor (HGF), pharmacokinetic measurements and effect APTT will be obtained in conjunction with the first and last ILB administration (Visit 2 and Visit 6). Blood samples will be obtained pre-dose, 30 minutes and 1, 2, 2.5, 3, 4, 6 hours after dosing. | |

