# INTRODUCTION

## Investigational background

Amyotrophic lateral sclerosis (ALS, also known as Lou Gehrig’s disease) is the most common motor neuron disease. It is a fatal disease, affecting most populations of neurons. The most important degeneration of neuronal cells occurs in motor neurons in spinal cord, brain stem and brain. The disease begins focally in the central nervous system and then spreads relentlessly[1]. The clinical diagnosis, defined by progressive signs and symptoms of upper and lower motor neuron dysfunction, is confirmed by clinical findings, electromyography, blood and cerebrospinal fluid (CSF) analysis. Additional testing with for instance Magnetic Resonance Imaging (MRI) excludes other conditions. The rate of progress of the disease is related to neuronal markers in CSF and blood. CSF levels of Neurofilament light chain (NFL) is the most important indicator of the activity of the disease [2-4]. The disease is heterogeneous, but most patients die of respiratory muscle weakness less than 3-5 years from symptom-onset. Like other age-related neurodegenerative diseases, ALS has genetic, metabolic and environmental triggers.

There is yet no cure for ALS, and management is focused on a combination of neuroprotective medication, multidisciplinary clinics and respiratory support. Speciality clinics for ALS emerged in the 1980s and most large centres in developed countries currently offer multidisciplinary care [5]. The disease causes severe decrease of the quality of life in both patients and next of kin [6-8]. Patients treated by ALS care teams may have higher quality of life [9] and longer survival [10]. Malnutrition and dehydration are common as ALS advances. Later therapy often includes percutaneous gastric feeding and non-invasive ventilatory support, which increases time of survival and increased quality of life of both patient and next of kin.

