### Criteria for permanent withdrawal

A subject will be permanently withdrawn from the study for the following reasons:

- Withdrawal of informed consent
- in case of pregnancy, planned pregnancy or non-compliance with set requirements for contraception
- if treatment with anticoagulants warfarin/NOAC is necessary
- concomitant treatment with Riluzole or Lamotrigine

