### in case of Serious Adverse Events (SAE) that are assessed as possibly or probably related to study treatment, including all risks categorized as of grade C (as stated in Appendix 1).

### Procedures for discontinuation of a subject from the study

A subject who prematurely discontinues participation in the study will always be asked about the reason(s) for discontinuation and the presence of any AEs. If possible, the patient will be seen by the investigator and assessed according to the procedures scheduled for the End-of-study follow-up (Visit 9). Any ongoing AE will if possible be followed as described in ‘Section 12.3.6’

In the event that a patient or their partner becomes pregnant in the period between Visit 2 and Visit 9, the outcome of the pregnancy should if possible be followed.

The reason and date the subject is removed from the study is to be documented in the Case Report Form (CRF) and in their medical records.

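### The lung-function withdrawal trigger has no direction, reference visit or confirmation, so one noisy FVC reading can end a patient's participation

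*Protocol*

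**What the plan says.** Section 9.6.3 is mandatory: "A subject will be permanently withdrawn from the study for the following reasons". The last item in its list covers SAEs judged at least possibly related to treatment, and then adds: "including all risks categorized as of grade C (as stated in Appendix 1").

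In Appendix 1, the lung-function row (microspirometer) defines grade C as "Variation >10% between time points". It does not say whether a rise counts, which visit is the reference, whether the 10% is relative or in points of percent predicted, or whether a repeat must confirm it. The treatment plan for that grade is "Observation/additional measurements and follow-up". In the bleeding row, grade C does instruct the site to stop ILB.

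The synopsis says "Respiratory function (FVC) will be evaluated at all visits". Table 2 shows this to be Visit 1a and Visits 2 to 9, nine readings in all. FVC is a secondary efficacy endpoint (section 7.2). Section 6.4 also gives a safety reason for measuring it, namely lung effects seen in rats.

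Section 9.6.4 assesses a discontinued patient by the Visit 9 scheme. On ECG the synopsis says "12-lead ECG will be obtained at Visit 1 and Visit 7". In Table 2 the CSF and blood biomarkers, including NFL, are taken only at Visits 1b and 7. Section 16.7 makes no correction for missing data.

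**The concern.** A threshold on variation between unspecified time points, applied to a test repeated nine times, can be crossed without any change in the patient. If crossing it means permanent withdrawal, measurement error decides who stays in the study. Sections 9.6.3 and Appendix 1 also point a site in different directions: one ends participation, the other asks for more measurements.

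A patient withdrawn by Visit 6 loses any remaining doses and Visit 7. Visit 7 holds the only post-dose ECG, which is a primary endpoint, and the only post-dose NFL and CSF samples. The Visit 9 scheme contains none of these, so the discontinuation visit does not recover them. With 15 patients and observed data only, a few such losses matter. FVC would also be selecting the patients in whom later FVC is summarised.

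**Working it through.** **Which reading does the text support?** On the broad reading, every grade C risk triggers withdrawal. On the narrow reading, grade C counts only when the event is also a related SAE. Two features favour the broad one:
- Section 9.6.1 attaches grade B to a discretionary ground in parallel wording, so grades B and C look like a ladder from optional to mandatory.
- Appendix 1 places an SAE at grade B in its last row, so grade C there is not a subset of SAEs.

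On the narrow reading, a 10% change in FVC is not in itself an SAE under section 12.2, so the clause adds nothing for lung function.

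**Inputs.** From the protocol: nominal days 1, 8, 15, 22, 29, 36, 50 and 99 for Visits 2 to 9; Visit 1a between day -30 and day -7; 15 patients; the 10% threshold. Assumed, because the protocol gives neither: within-patient CV of FVC 2 to 5%, and, for the selection effect only, a decline of 2 or 3% of the entry value per month with SD 2 between patients. The 10% is taken as relative.

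**Noise alone.** True FVC is constant and each reading is 1 + N(0, CV), independent between visits, with Visit 1a at day -18. The trigger is |later/earlier − 1| > 0.10. By the pre-dose reading at Visit 6 there are six readings. Simulation of 400,000 patients gives the share triggered by Visit 6:

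| Meaning of the time points | CV 2% | CV 3% | CV 4% | CV 5% | Expected of 15 |
|---|---|---|---|---|---|
| Against Visit 2 | 0.2% | 6% | 23% | 42% | 0.03 to 6.3 |
| Consecutive visits | 0.2% | 9% | 30% | 52% | 0.03 to 7.8 |
| Any pair | 0.6% | 18% | 49% | 72% | 0.1 to 10.8 |

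**Progression alone.** With linear decline and no noise, the monthly rate needed for a 10% fall is 10 / days × 30.4:
- Visit 2 to Visit 6 (28 days): 10.9% per month
- Visit 2 to Visit 7 (35 days): 8.7% per month
- earliest screening day to Visit 6 (59 days): 5.2% per month
- Visit 2 to Visit 9 (98 days): 3.1% per month

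Only the last is near the assumed 2 to 3% per month. It is reached at the final visit, where withdrawal costs no dose and no visit.

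**Selection effect on the Visit 9 FVC change.** This is the mean change in patients not triggered before Visit 9 minus the mean in all patients, with the assumed decline and CV 2 to 5%. The apparent decline is smaller by about 1.5 to 3 points for any pair, by about 0.7 to 2.1 points against Visit 2, and by about 0 for consecutive visits. The true mean change is about -6 to -10%.

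**The proposed rule.** Two independent readings at the same visit must both lie below 0.90 of the Visit 2 value. The share of unchanged patients meeting this by Visit 6 is under 0.1, 0.2, 1.8 and 5.2% for CV 2, 3, 4 and 5%.

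**The case against.** The grade C phrase follows a condition on related SAEs, and section 12.2 classes an event as unrelated when another cause explains it. An investigator could therefore set aside noise or progression. This stands as a possible reading, but the text does not settle it, and under it the lung-function row has no force in 9.6.3.

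A reader might infer that Appendix 1 flatly contradicts 9.6.3. That goes too far. The Appendix 1 column is a treatment plan, not a disposition rule. Platelet and allergic grade C do not mention stopping ILB either, and follow-up can continue after withdrawal. It is a tension.

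A reader might also infer, from the statement that "most patients die of respiratory muscle weakness less than 3-5 years from symptom-onset", that progression will remove many patients before Visit 7. The arithmetic does not support this.

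A sensitive lung trigger is defensible with a rat lung finding and a drug never given in more than two successive injections (section 8.2). That argues for a clear trigger, and for not letting ILB continue merely because ALS might explain a fall.

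The any-pair figures include screening. From Visit 2 onward they are 0.4, 13, 40 and 62%, and section 9.6.5 replaces patients who were never dosed. It also permits replacement of those withdrawn for reasons other than related AEs. Replacement restores numbers but does not undo selection. Finally, efficacy is secondary and descriptive, so no formal test is distorted.

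**Conclusion.** The point holds as a defect in how the rule is defined. Read literally, 9.6.3 with Appendix 1 permanently withdraws a patient for any unconfirmed FVC change above 10% in either direction. Read narrowly, it gives lung function no rule at all. Neither fits a parameter monitored for safety.

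The main route to lost doses and a lost Visit 7 is measurement noise. Its size depends on the unstated CV and on which time points are meant: negligible at 2%, and between 42 and 72% of unchanged patients by Visit 6 at 5%. Bias in the Visit 9 FVC mean change runs from about 0 to about 3 points, and is about 0 if consecutive visits are intended. The wording problem does not depend on these figures. The rule should be changed, but the documents do not show that the trial would lose a large share of its patients.

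**What to change.** In Appendix 1, define lung-function grade C as a fall of more than 10% relative to the pre-dose Visit 2 FVC, confirmed by a repeat measurement. Section 11 already allows repeat tests.

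In 9.6.3, state the consequence separately from the general grade C clause. Further ILB is stopped if the fall is confirmed and assessed as possibly related or related to ILB, with unclear cases counted as possibly related. The patient stays in the study for the remaining visits, including Visit 7 and Visit 9.

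The cost is a protocol amendment to two passages and an occasional repeat spirometry. The trigger also becomes slightly less sensitive, since a rise or an unconfirmed fall no longer counts. FVC is already measured before the first dose and at every later visit, so no new assessment is needed.
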